## 6. General Methodology

Medians, 25th and 75th percentiles will be presented for continuous variables; the number and percentage of patients in each category will be presented for nominal variables. Comparisons of continuous variables between the two randomized arms (anatomic versus functional diagnostic testing) (for example with respect to baseline characteristics) will be performed using the Wilcoxon rank-sum test, and comparisons of nominal variables will be performed using the chi-square test, unless otherwise specified. Appropriate statistical models and tests will be used to examine the effect of the testing strategies on the primary and secondary endpoints in the study. For time-to-event endpoints, the Cox proportional hazards model will be used unless specified otherwise. For comparing groups with respect to binary outcomes, logistic regression will be used. Statistical comparisons will be performed using two-sided significance tests. Additional perspective regarding the interpretation of the data will be provided through extensive use of confidence intervals and graphical displays, including plots of Kaplan-Meier event rate estimates. Analyses will be performed using SAS software version 9.2 or higher (SAS Institute, Inc., Cary, NC).

## 7. Endpoint Analyses

### 7.1 Primary Endpoint

The Primary Endpoint: Time from randomization to the first event in a composite of major cardiovascular events consisting of:

- Death (all-cause)
- Myocardial infarction
- Major complications from cardiovascular procedures and testing (stroke, major bleeding, anaphylaxis, and renal failure requiring dialysis)
- Unstable angina hospitalization

#### Response Variable Definition:

Time from randomization to the first event among the components of the primary composite endpoint is measured (in days) for those who experienced an event and is calculated as the date of the first event minus the date of randomization. For

patients who do not experience any of the component events or who withdraw consent or drop out of the study before it is complete, time from randomization to the date of last contact will be used in the analysis, and those patients will be considered as censored observations in the time-to-event analysis. All possible events are carefully reviewed and adjudicated by a clinical events committee (CEC) blinded to the randomized testing assignment. Definitions for each of the events are outlined in the study protocol as well as in the CEC charter. To qualify as an endpoint, the major complications from cardiovascular testing and procedures must occur during or within 72 hours following the test or procedure.

Statistical Methods: The Cox proportional hazards model (PROC PHREG in SAS) will be the primary analytic tool for assessing outcome differences between the two randomized arms with respect to the primary composite endpoint. To appropriately account for heterogeneity among the subjects, the primary analysis for comparing the diagnostic testing arms will involve covariate adjustment using the pre-specified baseline prognostic variables listed in Appendix A. A hazard ratio and 95% confidence interval (CI) summarizing the difference in outcome between the two randomized arms will be computed using the Cox model. The level of significance for the assessment of the primary endpoint will be  $\alpha=0.05$ .

In addition to the statistical hypothesis testing, cumulative event rates will be calculated according to the method of Kaplan and Meier for each randomized arm as a function of follow-up time (time from randomization), and the estimated event probabilities will be displayed graphically.

Given the relevance of clinical outcomes during the first year following non-invasive testing, and the study plan that all patients were to be followed for a minimum of 12 months, a comparison of the randomized arms based solely on the first 12 months of follow-up will be performed using the methods described above. For this analysis, patients not experiencing a primary event during the first year will have their follow-up censored after 12 months. The information from this analysis is only supplementary, however, to the primary comparison of the randomized arms, which is based on the total duration of follow-up available for each patient.

Non-inferiority Analysis: If the data (based on the entire follow-up experience) do not provide statistical evidence that the CTA testing strategy is superior to functional testing with respect to the primary endpoint, a test for non-inferiority of the CTA testing strategy will be performed. This assessment will be based on a pre-specified non-inferiority margin of 1.10 (expressed as a hazard ratio for CTA vs. functional testing). The non-inferiority assessment will be performed by comparing the upper limit of the two-sided 95% confidence interval for the hazard ratio with the non-inferiority margin. If the upper limit of the confidence interval falls below 1.10, non-inferiority will have been demonstrated. The p-value associated with the non-inferiority test will be reported as well. We emphasize that the superiority hypothesis will be assessed first, and if significant, the non-

inferiority assessment will not be performed. Only if superiority is not demonstrated will the non-inferiority analysis be performed.

## 7.2 Secondary Endpoints

The secondary endpoints for the study will be analyzed and interpreted in the order in which they are presented below.

### 7.2.1 Secondary Endpoint #1

Time from randomization to the first event in a composite consisting of the following:

- Each component of the primary endpoint
- Invasive cardiac catheterization without obstructive CAD (defined as no stenosis  $\geq 50\%$  in any major epicardial coronary artery, including side branches  $\geq 2\text{mm}$  in diameter, on the first catheterization performed  $\leq 90$  days following randomization)

Note: The obstructive CAD definition used in PROMISE is based on the Guideline and National Cardiovascular Data Registry definition aimed at identifying patients with anatomy suitable for either percutaneous or surgical revascularization. This definition is meant to represent the anatomic threshold for clinical action with respect to possible revascularization. In PROMISE, the classification of non-obstructive CAD is based on visual assessment and is adjudicated by a clinical events committee blinded to the randomized testing strategy.

The analysis of this secondary endpoint will be similar to and use the same methods as described for the primary endpoint in Section 7.1, including adjustment for the same set of covariates.

By definition, the only patients who can experience the component consisting of catheterization without obstructive CAD are those who undergo a cardiac catheterization within 90 days following randomization and meet the anatomic criterion defined above. All other patients (those who have a catheterization which reveals anatomically obstructive CAD, and those not undergoing cardiac catheterization within 90 days of randomization) will have the identical time to first event or censoring for this secondary composite endpoint as for the primary composite endpoint.

#### 7.2.1.1 Secondary Endpoint #1 – Alternate Definition of Non-Obstructive CAD

A supplementary analysis of secondary endpoint #1 will be performed using a definition of non-obstructive CAD which incorporates coronary pressure assessment (function) as measured by *fractional flow reserve* (FFR) where available. In this case, invasive cardiac catheterization without obstructive CAD for an individual patient is defined as  $\text{FFR} > 0.80$  for all major coronary arteries, or if catheterization was performed but FFR data are not available, the anatomic

criterion of <50% stenosis in all major coronary arteries as defined in 7.2.1 above will apply. With the exception of this alternate definition of non-obstructive CAD, each patient's time to their first event or censoring for this analysis will be calculated as in 7.2.1 above.

### **7.2.2 Secondary Endpoint #2**

Time from randomization to the first event in a composite of the following major clinical events:

- Death
- Myocardial infarction
- Unstable angina hospitalization

The analysis of this secondary endpoint will also use the same methods described for the primary endpoint in Section 7.1.

### **7.2.3 Secondary Endpoint #3**

Time from randomization to the first event in a composite of the following major cardiovascular events:

- Death
- Myocardial infarction

The analysis of this secondary endpoint will also be similar to the approach described for the primary endpoint in Section 7.1.

#### **7.2.3.1 Descriptive Comparisons of (a) Death, and (b) Myocardial Infarction**

Although the individual components of the primary and secondary endpoints listed above consisting of (a) death and (b) myocardial infarction are not specifically listed as secondary endpoints in the study protocol, the incidence of each of these components will be summarized and compared between the anatomic and functional testing arms to aid in the interpretation of the primary and secondary endpoint comparisons described above.

### **7.2.4 Secondary Endpoint #4**

Time from randomization to the first event in a composite of the following major complications from cardiovascular procedures or testing including:

- Stroke
- Major bleeding
- Anaphylaxis
- Renal failure requiring dialysis

In contrast to secondary endpoints 1 through 3, this particular endpoint and the comparisons between the randomized arms can be affected by the *competing risk* of death. For example, whether a patient experiences a stroke, major bleeding,

or any of the other component outcomes of this endpoint might be unobservable because the patient died before one of those events occurred. This can be problematic, particularly if there is a higher death rate in one randomized arm compared to the other arm. Therefore, the analysis of this endpoint will employ the competing risks methodology of Fine and Gray and make use of the cumulative incidence function (i.e., the marginal failure sub-distribution associated with the component events of this endpoint) rather than treating death as a censoring event and using the Kaplan-Meier method of estimating the event-rate function. (We note that in the presence of competing risks, the Kaplan-Meier method of estimating the event-rate function can be biased, because the assumption that a subject will experience the event of interest if the follow-up period is simply long enough is not appropriate.) The analysis of this endpoint will be performed using the proportional hazards model for the sub-distribution of interest, i.e., for modeling the cumulative incidence of the events comprising the components of this endpoint. This will be accomplished using the features of the Fine-Gray approach for handling competing risks data that are available as part of the PHREG procedure in the latest version of SAS. Assuming there is an adequate number of these major complications, the cumulative incidence functions for the two arms will be estimated, statistically compared, and graphically presented using these features in SAS. In addition, the cumulative incidence of each individual complication comprising this composite outcome will be tabulated to aid in the interpretation of any differences that emerge between testing strategies with respect to these major complications. Again we note that to qualify as an endpoint, the major complications from cardiovascular testing and procedures must occur during or within 72 hours following the test or procedure.

Finally, the competing risk analysis of this endpoint will be supplemented with further analyses by considering these major complications or death as a composite endpoint and using the same methodology as described in Section 7.1.

If the number of major complications proves to be small, the frequency in each randomized arm will be reported and compared with an appropriate two-sample test procedure such as Fisher's Exact Test.

### **7.2.5 Secondary Endpoint #5**

Incidence of:

- Invasive cardiac catheterization without anatomic obstructive CAD

This endpoint is defined in Section 7.2.1 above. By definition, the only patients who can experience this endpoint (catheterization without obstructive CAD) are those who undergo a cardiac catheterization within 90 days following randomization. All other patients (those who have a catheterization which reveals anatomically obstructive CAD ( $\geq 50\%$  stenosis), and those followed for at least 90 days after randomization who do not undergo cardiac catheterization in that time interval clearly do not meet this endpoint. Although the major interest is simply whether or not an invasive catheterization without obstructive CAD occurred within 90 days following randomization (irrespective of the timing when it occurred), the analysis can be complicated by the fact that some patients may die or withdraw consent prior to the 90-day time-point and therefore are not observable for the entire 90-day period. While the number of such patients is

expected to be small, they will be properly taken into account by using the Fine-Gray competing risk methodology described in section 7.2.4 above as implemented in the SAS procedure PHREG. Patients whose length of follow-up is more than 90 days (which will be most of the study patients) will be censored at 90 days in this analysis. The 90-day cumulative incidence rate of this event for each randomized arm will be calculated as part of the analysis to aid in the interpretation of the results.

#### **7.2.5.1 Secondary Endpoint #5 – Alternate Definition of Non-Obstructive CAD**

A supplementary analysis of secondary endpoint #5 will be performed using the alternate definition of non-obstructive CAD described in Section 7.2.1.1, which incorporates *fractional flow reserve* (FFR) where available. In this case invasive cardiac catheterization without obstructive CAD for an individual patient is defined as FFR>0.80 for all major coronary arteries, or if catheterization was performed but FFR data are not available, the anatomic criterion of <50% stenosis in all major coronary arteries as defined in Section 7.2.1 will apply. All other aspects of the analysis will be identical to the description in 7.2.5 above.

#### **7.2.6 Secondary Endpoint #6**

This is actually not a single endpoint, but rather a set of economic outcomes consisting of:

- Medical costs, resource use, and incremental cost effectiveness

The analytic approach to compare the economic impact of the two testing strategies will consist of two major parts, namely an empirical cost comparison of the testing strategies as randomized and a cost-effectiveness analysis. Primary statistical comparisons between the two randomized arms of empirical costs will include confidence limits around the observed cost differences constructed using bootstrap methods.

The cost-effectiveness analysis will estimate the incremental cost required to add an extra life year with the investigational anatomic arm relative to the control functional testing arm. In secondary analyses, we will incorporate utility weights to estimate the incremental cost per quality-adjusted life year gained with the CTA anatomic strategy, relative to the functional testing strategy. These analyses will be conducted from a societal perspective and will use a lifetime time horizon so that the estimated incremental cost-effectiveness and cost-utility ratios can be compared with societal benchmarks. We will also calculate within-trial cost-effectiveness/cost-utility ratios, although these ratios are limited in their value due to their failure to account for long-term benefits and costs and the absence of comparative benchmarks. Costs will be adjusted for inflation, and both costs and life expectancy will be discounted to present value at a 3% annual discount rate. Adjustments for censored data due to staggered entry will be made following the approach of Bang and Tsiatis. Extensive sensitivity analyses will be performed.

Additional details of the economic analyses will be described in a separate analysis plan prepared by the Economics and Quality of Life (EQOL) Coordinating Center at the Duke Clinical Research Institute.

### 7.2.7 Secondary Endpoint #7

- Cumulative radiation exposure

The radiation exposure endpoint (as described in Section 3.2) is defined as the cumulative radiation exposure from all cardiovascular diagnostic testing and procedures related to testing or management of atherosclerotic CAD and performed within 90 days following randomization. The testing and procedures will include CTA, stress nuclear imaging, diagnostic cardiac catheterization, and catheterization with percutaneous coronary intervention (PCI). For each patient, the amount of radiation exposure will be calculated as detailed below.

- a. For the initial diagnostic test (either CTA or stress nuclear imaging), radiation exposure for each patient was measured by the sites and documented by the Diagnostic Testing Coordinating Center (DTCC) using standard methodology.
- b. Radiation exposure for all subsequent diagnostic tests (CTA or nuclear imaging) will be estimated using multiple imputation based on the type of test performed, the CTA scanner or tracer protocol (if available), the radiation exposure as observed for the initial tests in the trial, and patient demographics.
- c. For patients undergoing cardiac catheterization, radiation will be estimated (imputed) based on data from the literature. The imputed value will depend on whether the catheterization was diagnostic only (in which case the imputed value will be 7mSv), or whether a PCI was performed (in which case the imputed value will be 15 mSv).

Handling Missing Data: Any patients with missing radiation data for the initial diagnostic test will have their exposure estimated using multiple imputation as in (b) above based on the diagnostic test received and the radiation exposure measurements available from the other patients. If a patient did not undergo any diagnostic test or cardiac procedure, their radiation dose will be zero.

Specific Analyses:

- (1) Comparison of the diagnostic testing arms as randomized with respect to *cumulative radiation exposure from all cardiovascular diagnostic tests and procedures* performed within 90 days following randomization. Patients who did not undergo either a diagnostic test or cardiac procedure within 90 days or who underwent a functional test with no radiation will be assigned an exposure value of zero.
- (2) Comparison of the diagnostic testing arms as randomized with respect to *radiation exposure of the initial diagnostic test* performed within 90 days following randomization. This comparison will include all randomized patients. Any patients who did not undergo either a CTA, a nuclear imaging test, or a cardiac catheterization as the initial diagnostic test performed within the 90-day period will be assigned an exposure value of zero.

- (3) Comparison of radiation exposure of the initial diagnostic test *according to the initial non-invasive test performed* (CTA vs. nuclear imaging). This comparison will be performed (i) in all patients whose initial diagnostic test was either CTA or nuclear imaging, and (ii) in patients undergoing either test in the randomization stratum consisting of patients where the enrolling site specified that if the patient was randomized to a functional test, stress nuclear imaging would be performed.

Statistical Methods: The distribution of cumulative radiation exposure in each randomized arm will be descriptively summarized (using means and standard deviations, medians, percentiles, and cumulative distribution functions) and statistically compared between the randomized arms and between different testing modalities using appropriate two-sample test methodology.

There is a sub-study within PROMISE on radiation exposure (PROMISE-SAFER) in which the radiation exposure data will be analyzed in greater detail. PROMISE-SAFER will have a separate analytic plan developed by the DCRI and the SAFER investigators at Columbia University.

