## **C5 *Rationale for Selection of Testing in Each Experimental Arm***

### ***Functional Testing Arm: Stress Nuclear, Stress Echo, and Exercise ECG***

Each of these procedures is a well-established and accepted strategy to diagnose CAD. Each has also been in routine clinical use for over 20 years and is well supported by class I, level of evidence B ACC/AHA practice guideline recommendations for use in suspected CAD. The guidelines further document specific indications as well as diagnostic and prognostic performance. (See also Table 2.) A national claims database (United HealthCare) documenting contemporary U.S. testing patterns shows that stress

---

nuclear exams constitute 61% of tests, with stress echo at 18% and exercise ECG at 21%. Computed tomographic angiography and stress magnetic resonance imaging comprised less than 1% each. Seventy-nine percent of tests were performed with exercise stress. The lack of a single dominant diagnostic strategy for current practice, even in this insured population, highlights the essential need for flexibility and breadth in the choice of functional tests to fully reflect real-world diagnostic practices and maximize generalizability and clinical impact. Thus it is essential that exercise ECG, stress echo, and stress nuclear imaging are all included in the functional testing arm.

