***Radiation Exposure Safety Endpoint***

Cumulative radiation exposure will be collected as follows:

- CTA: the actual administered dose (computed tomography dose index volume and dose length product for CTA) will be recorded by sites and confirmed by extracting information directly from the images.
- Nuclear imaging: the injected/administered contrast agent dose will be recorded and standard tables used to convert into equivalent doses for appropriate comparison with CTA.
- Invasive coronary angiography and intervention: the actual administered radiation dose or fluoroscopy time will be recorded by sites and standard tables used to convert into equivalent doses for appropriate comparison with CT.

These measures will ensure accurate calculation of the actual cumulative radiation exposure in each arm for tests performed for the diagnostic work-up during the 60 days following enrolment. In addition, we will capture all cardiac diagnostic testing involving radiation performed during the entire follow-up period (CTA, nuclear cardiology, catheterization) and will estimate cumulative radiation exposure over the entire trial using our original data collection (average dose per test for each site) to extrapolate radiation exposure during follow-up.

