## **2.d Analysis of Safety Events, Morbidity, Radiation Dose, and Incidental Findings**

The frequency with which major safety cardiac events occur (events other than the primary and secondary endpoints) will be carefully tabulated and descriptively summarized. Statistical comparisons of the randomized arms with respect to these events will use chi-square or other appropriate 2-sample methods, depending on the nature of the event, interpreting such comparisons in the context of differences between the 2 randomized arms in the primary and major secondary clinical endpoints and bringing to bear clinical judgment as to the relative seriousness of these events.

Of particular interest in this trial is the amount of radiation exposure to which subjects are subjected in each of the randomized arms of the trial. Radiation exposure for the various tests will be collected as elements of the electronic CRF (eCRF) and through the documentation of radiation exposure submitted to the DTCC. All cardiac diagnostic testing involving radiation exposure (e.g., CTA, stress nuclear, cardiac catheterization) performed during the entire follow-up period will be captured so that cumulative radiation exposure for each patient can be calculated. The distribution of radiation exposure in each arm will be summarized (using medians and percentiles) and compared between the randomized arms and different testing modalities using the Wilcoxon rank-sum test.

Incidental findings (e.g., such things as lung nodules) that may be discovered with the anatomic (CTA) testing strategy in contrast to the functional testing modalities will be captured as part of the data collection and tabulated descriptively.

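### SAP 7.2.7 gives every catheterization a fixed literature dose and stops counting at 90 days, contrary to protocol E4 and F2 2.d, and SAP section 17 lists neither change

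*Supplement*

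**What the plan says.** **Protocol Amendment 2.** E4 (Radiation Exposure Safety Endpoint) states that for invasive angiography and intervention "the actual administered radiation dose or fluoroscopy time will be recorded by sites and standard tables used to convert into equivalent doses". It then claims: "These measures will ensure accurate calculation of the actual cumulative radiation exposure in each arm", with the scope "for tests performed for the diagnostic work-up during the 60 days following enrolment". For the rest of the trial E4 does not claim measurement: it captures the tests and extrapolates from each site's average dose per test. D3 3.g permits modelled or literature values, but only when site information cannot be had or is judged untrustworthy. F2 2.d says that cardiac tests involving radiation "performed during the entire follow-up period will be captured so that cumulative radiation exposure for each patient can be calculated", and it names medians, percentiles and the Wilcoxon rank-sum test. E2 has interval radiation exposure assessed at each six-monthly contact.

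**SAP 7.2.7.** Item (a) keeps the measured dose for the initial CTA or nuclear test. Item (b): "Radiation exposure for all subsequent diagnostic tests (CTA or nuclear imaging) will be estimated using multiple imputation". Item (c): "For patients undergoing cardiac catheterization, radiation will be estimated (imputed) based on data from the literature", at 7 mSv for a diagnostic procedure and 15 mSv with PCI. The endpoint covers the first 90 days after randomization. The arms are to be "statistically compared between the randomized arms and between different testing modalities using appropriate two-sample test methodology".

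**SAP sections 6, 17 and 18.** Section 6 makes the Wilcoxon rank-sum test the default for continuous variables unless something else is specified. Section 17, the list of changes from the protocol, does not mention radiation. Section 18 places radiation safety among the results that carry the trial's interpretation.

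**The concern.** Two features of the protocol's endpoint change in the SAP without being declared.

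The first is the source of the dose. A conditional fallback becomes the rule for every catheterization, and imputation becomes the rule for every later CTA or nuclear test. A single constant carries no patient-to-patient variation and no uncertainty about its own value. Any error in it enters the arm comparison in proportion to the difference in catheterization or PCI rates. Those procedures lie downstream of the randomized test, so their rates may well differ between the arms.

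The second is the window. Repeat testing after 90 days is left out, with no supplementary analysis to recover it. Yet the protocol argues in C5 that CTA results stay valid for longer, which bears directly on later testing and its radiation.

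**Working it through.** **Step 1: the texts side by side.**

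| Exposure | Protocol Amendment 2 | SAP 7.2.7 | Listed in SAP section 17? |
|---|---|---|---|
| Initial CTA or nuclear test | Recorded (E4) | Measured | No change to list |
| Catheterization/PCI in the 60-day work-up | Recorded dose or fluoroscopy time, converted (E4); literature only as fallback (D3 3.g) | 7 or 15 mSv for all | No |
| Later CTA/nuclear in the 60-day work-up | Recorded (E4); same fallback | Multiple imputation for all | No |
| Days 61–90 | Captured, extrapolated from the trial's own site averages (E4) | Constants or imputation | No |
| After day 90 | Captured, extrapolated (E4, F2 2.d) | Not counted | No |

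The sharpest conflict is over catheterization in the work-up window. For later CTA and nuclear tests, imputation from the trial's own initial-test doses is close to what the protocol does after day 60, so that conflict is confined to the work-up. Item (b) carries imputation uncertainty because it is multiple imputation; item (c) carries none.

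**Step 2: how much an error in the constants could matter.** There is no figure in the plan to reproduce: no power or precision is stated for this endpoint, and no catheterization or PCI rates are given. The rate differences below are assumptions.

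Contribution to the mean difference = (rate difference) × (constant). Shift from a 50% error = (rate difference) × 0.5 × (constant), that is, 3.5 mSv or 7.5 mSv times the rate difference.

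| Assumed rate difference | Diagnostic, 7 mSv: contribution / shift | PCI, 15 mSv: contribution / shift |
|---|---|---|
| 2 points | 0.14 / 0.07 mSv | 0.30 / 0.15 mSv |
| 4 points | 0.28 / 0.14 mSv | 0.60 / 0.30 mSv |
| 8 points | 0.56 / 0.28 mSv | 1.20 / 0.60 mSv |

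With equal rates the shift is zero.

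For scale, take the protocol's claims-data mix ("nuclear exams constitute 61% of tests"; echo and exercise ECG carry no dose) and 12 mSv per nuclear test, the midpoint of the 7–17 mSv range in D3 3.g. The functional arm's first-test mean is then 0.61 × 12 = 7.3 mSv. The shifts run from 0.07/7.3, about 1%, to 0.60/7.3, about 8%.

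**Step 3: does the choice of summary matter?** Under the same mix, the functional-arm median is the (0.50 − 0.39)/0.61 = 18th percentile of nuclear dose. With an assumed coefficient of variation of 25% for nuclear dose, that is 9.3 mSv by simulation, against a mean of 7.3. If CTA averaged 8 mSv (also CV 25%), the mean difference would be +0.68 mSv (CTA higher), while the probability that a CTA patient's dose exceeds a functional patient's would be 0.472 (CTA lower). The mean and the Wilcoxon test disagree only for a CTA mean of about 7.3–8.6 mSv. Outside it they agree:

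- CTA and nuclear both uniform on 7–17 mSv: means 12.0 v 7.3, medians 12.0 v 8.8, CTA higher on both.
- CTA uniform on the reduced range of 2–6 mSv: means 4.0 v 7.3, medians 4.0 v 8.8, CTA lower on both.

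**The case against.** The best defence is that the protocol is itself part estimate. It claims actual doses only for the work-up, extrapolates afterwards and allows literature values. The SAP says only that initial-test doses were measured, and nothing shown proves that catheterization doses reached the database in usable form. A separate PROMISE-SAFER plan, not shown, is to analyse radiation in more detail. Constants given to a catheterized minority should also move a rank test less than they move a mean. All of this limits the size of the problem. None of it explains why 7.2.7 drops the condition in D3 3.g. If the site data proved unusable, that condition is met and section 17 is the place to say so. A sub-study plan does not redefine an endpoint that this SAP defines and section 18 relies on.

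A reader might infer two stronger points, and the documents support neither:

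- *That measured doses are replaced across the board.* Item (a) keeps them for the initial CTA or nuclear test.
- *That the arm comparison is left open, so mean and median could be chosen to give opposite answers.* Protocol F2 2.d names the Wilcoxon test with medians and percentiles, and SAP section 6 makes Wilcoxon the default. The reversal in step 3 needs a narrow CTA dose range and a spread that the documents do not give. What remains is that 7.2.7 does not repeat the test's name, and its loose wording could be read as overriding the default.

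**Conclusion.** The point holds in bounded form. SAP 7.2.7 departs from the protocol on the source of catheterization and later-test doses and on the follow-up window, and section 17 declares neither. The discrepancy rests on the text alone.

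Its numerical effect rests on assumptions. For rate differences of 2–8 points and a 50% error in the constant, the shift in the mean difference is 0.07–0.28 mSv for diagnostic catheterization and 0.15–0.60 mSv for PCI, in a direction that cannot be known in advance. The effect of stopping at 90 days cannot be sized from the documents. There is no case for replacing the protocol's Wilcoxon test with a mean difference.

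**What to change.** - **Dose source (7.2.7 b and c).** For catheterization, PCI and later tests, use the recorded dose or converted fluoroscopy time where available. Keep imputation and the 7 and 15 mSv constants as the fallback, and vary the constants over a stated range in a sensitivity analysis.
- **Window.** Keep the 90-day endpoint if preferred, and add a supplementary comparison of cumulative exposure over the whole of follow-up, using the protocol's extrapolation.
- **Test.** Name the Wilcoxon rank-sum test with medians and percentiles in 7.2.7, and label means descriptive.
- **Section 17.** List the dose-source and window changes with reasons. If catheterization doses were not obtained in usable form, say so there.

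The cost is a little more programming and slightly wider intervals. No new data are needed beyond what the protocol already plans to collect.
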